**PROTOCOL ( Alternative Second part)**

Leave "Multi-electrode lead" (postero)lateral vein position  
Add a second lead in the posterior or anterior vein

Start RA-pacing (100 bpm or otherwise highest tolerable rate)

(A) Pacing @ distal electrode. Make sure capture is obtained. If yes, run pacing protocol

(B) Pacing @ mid electrode. Make sure capture is obtained. If yes, run pacing protocol

(C) Pacing @ proximal electrode. Make sure capture is obtained. If yes, run pacing protocol

(D) Simultaneous pace @ all three electrodes  
Run pacing protocol

## E Pacing protocol

## Pacing protocol

- Program optimal AV delay
- Turn pacing 'on' via connection box during 10-15 sec
- Turn pacing 'off' via connection box during 10-15 sec
- Repeat ON/OFF 3 times (so 4 times in total)
- Program other AV delays (+/- 20 ms & +/- 40 ms) and repeat pacing protocol

[figure not shown]

**Figure 4: Description of the pacing protocol.** In A the start of the protocol is depicted which involves imaging of the venous anatomy of the patient. The protocol can be separated into two parts, depending on the patient's anatomy. Part B is similar for every patient while part C or D is patient-dependent. In general, one part consists of BiV or Multivein using one or both of two opposite coronary veins (multivein approach). The other part consists of using up to three LV electrodes (BiV or QuadV) to pace from the (postero)lateral vein (multispot approach). Part E is displaying the pacing procedure for 1 out of total 5 AV delays during which the positive  $dP/dt_{max}$  will be measured. Each setting, as indicated by a horizontal line in the figure, will last 10-15 sec. The repetition of steps is used to increase sensitivity of the positive  $dP/dt_{max}$  measurements. Five AV delays will be assessed: optimal AV, optimal AV delay +/- 20 and +/- 40 ms.

At each pacing site, the evaluation of the effect of CRT will be performed approximately 4 times (repetition) in order to increase signal to noise ratio. Each setting lasts about 20 beats (10-15 sec) interspersed with baseline (AAI; also 20 beats, 10-15 sec) pacing. The heart rate will be elevated by atrial pacing to a base rate to 100 bpm or maximally tolerable rate (less than 10% drop in  $dP/dt_{max}$  from baseline no pace), to ensure a constant heart rate. The RV-LV (= VV-timing) intervals will be zero. Optimal AV-delay will be calculated using formulas ( $PAV_{ECG} = \min \{Ap-Pend + 30 \text{ ms}, Ap-RVs - 50 \text{ ms}\}$ ) derived

from a correlation study between electrocardiographic measures such as the intrinsic AV interval and P-wave duration. The method aims at absence of truncation of the E/A waves. Up to five different AV-delays will be evaluated in this study (i.e. the optimal AV-delay and optimal AV-delay  $\pm$  20 and  $\pm$  40 ms). Hemodynamic measurements of positive LV dP/dt max, LV End diastolic pressure, arterial pressures, and stroke volume derived from arterial pressure will be measured during baseline and CRT. Additionally, at each pacing setting, the electrical delay from RV-pace to the different LV activations will be measured.

The signals from the LV pressure catheter, finger plethysmography device, internal electrograms, and surface ECG will be collected in real time and stored for later analysis as explained earlier (section 4.3). The CRT implant or EP-procedure will be completed as per standard practice.

Protocol procedures are anticipated to last about 60 to 120 minutes. Pacing will be achieved by using a Medtronic 2290 analyzer and temporary pacemaker (5388) stimulators or equipment present in the OR of the participating physicians.

Sponsor representatives (e.g. Field Clinical Engineer, Field CRS, Technical Consultant) may be delegated to perform certain study related activities such as technical support during procedures and data collection. Documentation of study training and qualification of sponsor representatives will be maintained by Medtronic.

## 7.5 Subject Exit and Withdrawal

Study Exit is defined as the moment when a subject officially stops participating in the study. The date and reason for subject exit must be reported to Medtronic at the earliest opportunity.

Reasons subject may be exited from the study include, but are not limited to:

- Study completion
- Subject did not provide consent
- Subject did not meet inclusion/exclusion criteria
- Subject chooses to withdraw (e.g., consent withdrawals, relocation to another geographic location)
- Investigator deems withdrawal necessary (e.g., medically justified, inclusion/exclusion criteria not met, failure of subject to maintain adequate study compliance)
- Subject death

Subjects will be exited from the study just before the moment of hospital discharge. This will be documented on the Study Exit CRF. There will be no further follow-up required for subjects that are exited from the study since no investigational products will be implanted or used in the study.

### **7.5.1 Subject Initiated Withdrawal**

A subject will be exited from the study in the event that he or she is unable to participate, expresses a desire to withdraw, or is unwilling to continue participation in the study. The reason for withdrawal needs to be documented in the patient chart. The subject should be informed that their future care or treatment will not be affected in any way as a result of choosing to not participate in this study. Furthermore, alternative treatments and medical consequences of exiting the study should be discussed with the subject. Any significant new findings related to the study that may develop, which may relate to the subject's willingness to continue participation, should be communicated to the subject. Unless the patient explicitly revokes informed consent, available data will be reported.

### **7.5.2 Investigator Initiated Subject Withdrawal**

A subject may be exited from the study if an investigator feels it is necessary to withdraw the subject from the study due to a medical condition or other reason. In such cases, the subject will be notified and provided an explanation regarding the reasons for the study exit. Unless the patient explicitly revokes informed consent, available data will be reported.

## **7.6 Overview of Data Collection Requirements**

Clinical data will be collected at enrollment and during the study procedure. Clinical data to be collected may include but is not limited to: demographics, medical history, cardiovascular medications, multi-lead ECG, pregnancy test, digitally stored echo images, digitally stored MRI images, chest X-ray, non-invasive blood pressure monitor data, invasive blood pressure data, LV pressure data, and unipolar/bipolar electrograms. Table 4 summarizes the data requirements.

**Table 4: Data Collection Requirements**

|                                                                              | Enrollment | Study day |
|------------------------------------------------------------------------------|-------------------|------------------|
| Inclusion/Exclusion Criteria                                                 | ✓                 |                  |
| Subject Informed Consent                                                     | ✓                 |                  |
| Demographics, medical history, CV medication, pregnancy test (if applicable) | ✓                 |                  |
| MRI (structural and hemodynamic)                                             | ✓                 |                  |
| NYHA class                                                                   | ✓                 |                  |
| LVEF                                                                         | ✓                 |                  |
| Surface ECG                                                                  | ✓                 | ✓                |
| Blood chemistry                                                              | ✓                 |                  |
| Venogram                                                                     |                   | ✓                |
| Non-invasive blood pressure                                                  | ✓                 | ✓                |
| Invasive blood pressure                                                      |                   | ✓                |
| LV pressure                                                                  |                   | ✓                |
| LV lead implant location (Chest x-ray)                                       |                   | ✓                |
| Unipolar and Bipolar electrograms                                            |                   | ✓                |
| Adverse events                                                               |                   | ✓                |
| Deviation Collection (as indicated, Section                                  | ✓                 | ✓                |
| Exit                                                                         |                   | ✓                |

## 8 Statistical Method and Data Analysis

### 8.1 Sample Size Justification

This study is powered for non-inferiority for the primary end point of difference in percentage change dP/dt max from baseline between Biventricular (BiV) pacing and Quadri-ventricular (Multispot) pacing. This is calculated as [percentage change in dP/dt max during Multispot] - [percentage change in dP/dt max during BiV]. Non-inferiority will be declared if the lower limit of a 1-sided 97.5% confidence interval of difference does not fall below -4%. Assuming the expected difference in percentage change dP/dt max between BiV pacing and multispot pacing is 0% and a standard deviation in differences of 8%, 34 patients would have 80% power to demonstrate non-inferiority for dP/dt max. The total sample size is increased to 40 patients to accommodate for non-compliance with protocol. Superiority testing will be performed if non-inferiority is met.

$$\begin{aligned}H_0: \Delta_{\text{multispace}} - \Delta_{\text{BiV}} &\leq -4\% \\H_1: \Delta_{\text{multispace}} - \Delta_{\text{BiV}} &> -4\%\end{aligned}$$

Previous literature suggests the average mean difference in percentage change between BiV and no pacing is 18%, in this study we consider Multispace non-inferior to BiV if the difference in their means is less than a quarter of the difference between BiV and no pacing [34]. No literature is available on the standard deviation of differences, which is the variability of the difference between pacing configurations within each subject. However we estimate that it would be less than half the variability seen when comparing differences across different patients.

## 8.2 Study Endpoint

During the study all hemodynamic and electrophysiological data is continuously collected. The primary endpoint for this study is the positive dP/dt max value during BiV pacing and Multispace pacing. These data will be calculated offline using pre-determined filter-settings and algorithms. The values will be obtained on a beat-to-beat basis. To reduce variance, in particular the positive dP/dtmax values, each pacing setting is repeated 4 times. A similar approach will be taken for the (non)-invasive secondary endpoints.

## 8.3 Analysis Methods

Descriptive statistics will be used to summarize the patient demographic and clinical characteristics at baseline. Data for qualitative variables will be presented as incidence rates (total number of patients, number of events, and percent). Data for continuous variables will be summarized using measures of central tendency and dispersion.

To calculate the mean LV dP/dt max difference and 95% confidence interval between pacing configurations a restricted maximum likelihood (REML)-based repeated measures approach (MMRM) will be used. Analyses will include the fixed, categorical effects of center (if sufficient number of patients per center available), pacing configuration, AV delay and if possible heartbeat. If the model is unable to support the beat-to-beat dP/dt values (i.e too much variability in the number of beats available per AV delay) then they will be averaged. The within-patient errors will be modelled using an unstructured (co) variance structure. If this analysis fails to converge, auto regressive, toeplitz, compound symmetric, and simple structures, with and without heterogeneous variances by pacing configuration will be tested. The (co)variance structure converging to the best fit, as determined by Akaike's information criterion, will be considered the primary analysis. Significance tests will be based on least-squares means and Type III sum-of-squares. Analyses will be implemented using SAS PROC MIXED.

Correlation coefficients will be calculated for each of the (non)-invasive measures with LV dP/dt, to account for the repeated measurements a linear mixed effects model will be used. Additional, a categorical variable of the best pacing configuration per patient will be calculated (the configuration that achieves the largest dP/dt value) and the agreement with each (non)-invasive

evaluation of best pacing configuration (also derived into a categorical variable) will be evaluated and tested with an unweighted Kappa statistic.

P-values will be evaluated based on a two-sided significance level of 0.05, and interaction effects will be evaluated at a significance level of 0.10. Except for the primary objective which is evaluated using a one-sided significance level of 0.025. No adjustments will be made for multiple testing. No imputation of missing data is planned.

Any change to the data analysis methods described in the Clinical Investigational Plan will require an amendment only if it changes an objective of the Clinical Investigational Plan. Any other change to the data analysis methods described in the Clinical Investigational Plan, and the justification for making the change, will be described in the clinical study report. Additional exploratory analyses of the data will be conducted as deemed appropriate.

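### The primary mixed model in 8.3 leaves out the patient-by-configuration variation behind n = 34, so its confidence interval depends on the covariance structure selected and can be too narrow

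*Combined protocol and SAP*

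**What the plan says.** Section 8.1 bases the sample size on a within-patient difference in percentage change of dP/dt max: "a standard deviation in differences of 8%, 34 patients would have 80% power". The assumed true difference is nil ("the expected difference in percentage change dP/dt max between BiV pacing and multispot pacing is 0"). Non-inferiority requires that the "lower limit of a 1-sided 97.5% confidence interval of difference does not fall below -4"%.

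Section 8.2 says of the dP/dt max data: "The values will be obtained on a beat-to-beat basis". Each setting is repeated four times.

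Section 8.3 fits a REML repeated-measures model with fixed effects for center (if numbers allow), pacing configuration, AV delay and possibly heartbeat. Its first-choice covariance is clear: "The within-patient errors will be modelled using an unstructured (co) variance structure". The next step is: "If this analysis fails to converge, auto regressive, toeplitz, compound symmetric, and simple structures", each with and without heterogeneous variances. The converging structure with the best AIC becomes the primary analysis. Beat values are averaged if the model cannot support them, and the example given is uneven beat counts across AV delays. Section 8.3 sets the primary test apart: "Except for the primary objective which is evaluated using a one-sided significance level of 0.025".

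**The concern.** Patients differ in how much better or worse they do with Multispot than with BiV. Extra beats or AV delays from the same patient do not average that variation away; only more patients do. An interval for the mean difference must therefore carry a patient-by-configuration component, and 8.3 names none. An unstructured matrix would absorb it. The fallback structures do so only partly or not at all, and they differ widely in the standard error they give the same contrast. AIC ranks them on overall fit, not on whether that standard error is right.

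This one interval decides non-inferiority and opens the superiority test. If it is too narrow, both claims carry more than the stated one-sided 2.5% error. The closing paragraph of 8.3 also allows methods to change without an amendment unless an objective changes, so the structure could be settled after the data are seen.

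**Working it through.** **Inputs from the documents.** Margin −4, SD of differences 8, n = 34 evaluable and 40 enrolled, one-sided 0.025 (8.1, 8.3); 7 settings in 3 configurations (section 2); 5 AV delays, 4 repeats, about 20 beats each (7.4.2); about 8 centers (6.3).

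**1. The plan's own figure.** The normal formula gives ((1.96 + 0.84) × 8/4)² ≈ 31.4, so 32. The paired t calculation gives 34, with power 0.808. So n = 34 is the sample size of a paired t analysis with standard error 8/√34 = 1.37. The 95% half-width is 2.79 at n = 34 and 2.56 at n = 40.

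**2. Size of the unstructured matrix,** d(d + 1)/2 parameters:

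| Repeated unit | d | Parameters |
|---|---|---|
| 2 configurations × 5 AV delays | 10 | 55 |
| 3 × 5 | 15 | 120 |
| 7 settings × 5 | 35 | 630 |
| 7 × 5 × 20 beats | 700 | 245,350 |
| with 4 repeats | 2,800 | 3,921,400 |

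Beat level is out of reach. At d = 35, 34 patients leave 34 − 1 = 33 degrees of freedom, and 40 patients with 8 center effects leave 40 − 8 = 32. Both are below 35, so the matrix is singular. With 40 patients and no center effects, 39 just exceeds 35. At d = 10 and 15 the model was fitted at n = 34 in simulation. Its standard error was 0.84-0.90 of the true one at d = 10 (one-sided error 0.030-0.043) and 0.78-0.79 at d = 15 (0.060-0.062).

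**3. Compound symmetry, analytically.** Let σg² be the patient-by-configuration variance, σe² the residual variance, m the readings per configuration and J the configurations. Then

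(model SE / true SE)² = [σe² + σg²·m(J − 1)/(Jm − 1)] / [m·σg² + σe²].

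The variance of a patient's difference is 2(σg² + σe²/m) = 64, so σg² + σe²/m = 32. Write f = σg²/32 for the share due to patient-by-configuration variation; the documents do not give f. For J = 2, m = 5, f = 0.5: σg² = 16 and σe² = 5 × 16 = 80. The squared ratio is (80 + 16 × 5/9)/(80 + 80) = 0.556, so the ratio is 0.75. The error is P(Z > 1.96 × 0.745) = 0.072, and 34 patients count as 34/0.556 = 61.

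| f | SE ratio, m = 5 | One-sided error |
|---|---|---|
| 0 | 1.00 | 0.025 |
| 0.25 | 0.88 | 0.042 |
| 0.5 | 0.75 | 0.072 |
| 0.75 | 0.58 | 0.129 |
| 0.9 | 0.45 | 0.190 |

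**4. The planned rule, by simulation.** REML fits at n = 34 with fixed effects for configuration and AV delay, and AIC choosing among the fallbacks. Assumptions: between-patient SD 16, balanced data, readings ordered by configuration then AV delay, t with n − 1 degrees of freedom. There were 400 runs per scenario at 5 readings per configuration.

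| Analysis (5 readings) | SE ratio | One-sided error |
|---|---|---|
| Paired t | about 1.0 | 0.015-0.033 |
| Simple | 1.40-1.57 | below 0.01 |
| AR(1) | 1.13-1.86 | below 0.01 |
| Toeplitz | 0.74-0.95 | 0.030-0.075 |
| AIC choice, f = 0 | 0.97 | 0.028 |
| AIC choice, f = 0.5-0.9 | 0.75-0.83 | 0.045-0.070 |
| AIC choice, f = 0.5, patient-by-AV SD 6 added | 0.93 | 0.030 |

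With 20 readings (60 runs only), AIC choice gave ratios of 0.78 at f = 0.5 and 0.70 at f = 0.75, with error about 0.05-0.08. On the 7 × 5 grid (60 runs, homogeneous structures only, f = 0.5-0.9) the AIC-chosen standard error averaged 1.15-1.20 against 1.37, which implies an error of about 0.04-0.05. At f = 0.9 on that grid the mean standard errors were 0.69 (compound symmetric), 1.15 (Toeplitz), 1.86 (simple) and 3.49 (AR). That is a fivefold spread for one contrast.

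Monte Carlo error matters: at a true 6% it is √(0.06 × 0.94/400) = 1.2 points for 400 runs and 3.1 points for 60.

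**The case against.** The strongest defence is that 8.3 allows averaging and names pacing configuration, not setting, as the model factor. On that reading the matrix has dimension 10 or 15, the unstructured model fits, and the fallback list may never be used. This stands in part: a reader might infer from the 35-cell layout that an unstructured covariance is impossible and fallback near certain, but the documents do not fix the dimension. The defence is incomplete, though. The averaging clause is tied to uneven beat counts, so with even counts the plan could stay at beat level and go straight to the fallbacks. And the unstructured fit at 10 or 15 dimensions is itself too narrow without a small-sample correction.

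A reader might also infer that every fallback counts readings as independent replicates and makes the interval far too narrow. That does not hold. On averaged cells, simple and AR(1) are too wide, and Toeplitz is only moderately narrow. The larger errors in step 3 (0.129 and 0.190) need compound symmetry to be kept at f of 0.75-0.9. In the two-configuration runs with 5 readings, AIC chose a Toeplitz form in 370 of 400 at f = 0.75 and in all 400 at f = 0.9.

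Finally, the 8% is a total SD that includes measurement noise, so f could be small. That cannot be excluded. Still, with five readings f = 0 needs a residual SD of √160 = 12.6 points in cell means of about 4 × 20 = 80 beats, and f = 0.5 needs √80 = 8.9. Section 8.1 puts the average BiV effect itself at 18%. Section 3 also cites marked differences between individuals in the best site. These points favour a larger f but do not establish one.

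**Conclusion.** The concern holds in a limited form. The analysis in 8.3 does not match the per-patient basis of 8.1, and the width of the primary interval depends on a structure chosen for fit. The AIC rule leaves the nominal 2.5% essentially intact if there is no patient-by-configuration variance. It takes the error to about 4-8% if that variance is at least half of the variance of differences, or to about 3% at f = 0.5 if there is also substantial patient-by-AV variation. The share f, the between-patient SD of 16 and balanced data are assumptions, and the upper end of the range rests on few runs. The documents do not support a claim that the interval is always, or far, too narrow. The study is exploratory and its recordings do not guide care, but this interval carries its only powered conclusion and the repair is cheap.

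**What to change.** For the primary analysis, reduce each patient's data to one percentage change for Multispot and one for the reference BiV setting. Average over beats and the four repetitions, and prespecify one handling of the AV delays. Two options are the calculated optimal delay, which agrees with the definition of standard BiV in 6.1, or the mean over all five. Report the per-patient difference with a paired t confidence interval against the −4% margin.

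If a mixed model is preferred, for example to cover all settings, define the repeated unit, include random patient and patient-by-setting effects, and state Kenward-Roger degrees of freedom. In either case, remove the rule that lets AIC choose the structure behind the primary interval.

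The cost is a rewording of 8.3, with no extra patients or measurements. The interval may be wider than the selected model would have given (or narrower, had simple or AR(1) been selected), but it has the width that n = 34 already assumes.

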The veins will be accessed using EP-catheters or currently used coronary sinus over the wire (OTW)-pacing leads. Once the three configurations have been evaluated the investigational procedures will end and the EP/CRT-implant-procedure will continue as per standard practice.

Non-invasive sensor data include the measurements of arterial pressure performed by finger plethysmography and the surface ECG. Invasive sensor data will be derived from the electrocardiogram timing, i.e. the electrical delay between the RV and/or different LV sites from the implanted leads/catheters. These measurements will be correlated with positive LV dP/dt max to determine the feasibility of using them to guide LV lead placement. Optional, also invasive blood pressure will be collected.

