#### 6.2.2 Secondary Objectives

The secondary objectives of this study are to:

- Compare the positive LV dP/dt max from the multi-vein LV pacing configuration to the standard single spot LV pacing.
- Compare the positive LV dP/dt max from the multi-vein LV pacing configuration to the multispot LV pacing.

- Correlate the (non)invasive measures (blood pressure, electrocardiographic mapping and RV/LV EGM timings) obtained during the three pacing configuration's to the positive LV dP/dt max measures obtained.
- Evaluate the non-invasive measures ability to identify the pacing configuration with the highest positive LV dP/dt max.
- Evaluate the within patient variability in positive LV dP/dt max measures.

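### The sensor–dP/dt correlation in 8.3 does not separate within-patient from between-patient association, although guiding lead placement needs the within-patient one

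*Combined protocol and SAP*

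**What the plan says.** The analysis is given in one sentence of 8.3 Analysis Methods: "Correlation coefficients will be calculated for each of the (non)-invasive measures with LV dP/dt", and "to account for the repeated measurements a linear mixed effects model will be used". The sentence does not name the scale of either variable, the random effects, the fixed effects, or how a correlation coefficient is taken from the model. The matching objective in 6.2.2 relates the sensor measures "to the positive LV dP/dt max measures obtained".

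The purpose is in 2 Study Summary: "These measurements will be correlated with positive LV dP/dt max to determine the feasibility of using them to guide LV lead placement".

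Two other parts of the plan bear on this. The next sentence of 8.3 sets up a separate agreement analysis, in which "a categorical variable of the best pacing configuration per patient will be calculated" and compared by unweighted kappa with the best configuration according to each sensor. Section 8.1 defines the primary comparison as the "difference in percentage change dP/dt max from baseline between Biventricular (BiV) pacing and Quadri-ventricular (Multispot) pacing".

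**The concern.** Choosing a pacing site means ranking the options in one patient. The relevant question is whether, when the sensor reading rises from one setting to another in the same patient, dP/dt max rises too. Whether patients with high sensor readings also tend to have high dP/dt max is a different question and does not help to place a lead.

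A mixed model fitted to repeated values from many patients contains both associations. Unless they are given separate terms, the reported coefficient is a blend, with weights that depend on the variance split and the number of values per patient. A sensor that ranks settings well could look weak, or one that only separates patients with better and worse contractility could look informative. Either would misdirect the feasibility conclusion for this objective.

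**Working it through.** **Inputs from the documents.** There are 7 pacing settings (section 2) and 5 AV delays (7.4.2), so up to 7 × 5 = 35 setting-by-delay values per patient. The design has 34 evaluable patients (8.1), and secondary tests are two-sided at 0.05 (8.3). The plan gives no figure for the sensor correlations. The 34 itself reproduces: a paired test with margin 4, SD 8, true difference 0 and one-sided 0.025 has 79.5% power at 33 patients and 80.8% at 34 (noncentral t).

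**Assumptions.** The documents give no between- or within-patient variances. I took the between-patient share of variance (ICC) as 0.5, 0.8 and 0.9, equal for sensor and dP/dt. Values are independent given the patient. rB and rW are the between- and within-patient correlations.

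**Case 1: a total correlation of levels is reported.** Then r_total = ICC × rB + (1 − ICC) × rW.

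| rB | rW | ICC 0.5 | ICC 0.8 | ICC 0.9 |
|---|---|---|---|---|
| 0 | 0.6 | 0.30 | 0.12 | 0.06 |
| −0.5 | 0.6 | 0.05 | −0.28 | −0.39 |
| 0.7 | 0 | 0.35 | 0.56 | 0.63 |

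For example, at ICC 0.8: 0.8 × 0 + 0.2 × 0.6 = 0.12, and 0.8 × 0.7 + 0.2 × 0 = 0.56. Masking and mimicking both occur across the whole range.

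**Case 2: an uncentred slope from a random-intercept model.** Scale both within-patient variances to 1, so that the within-patient slope equals rW and the between-patient variance is ICC/(1 − ICC), which is 4 at ICC 0.8. The fitted slope is a weighted mean of the within-patient slope and the slope on patient means.

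Mimicking, rB = 0.7, rW = 0, ICC 0.8:
- 7 values: slope on means = (4 × 0.7)/(4 + 1/7) = 0.676; between-patient weight 0.164; fitted slope 0.676 × 0.164 = 0.111 instead of 0.
- 35 values: (4 × 0.7)/(4 + 1/35) = 0.695; weight 0.029; fitted slope 0.020.

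These biases are small, but the standard error is small too. Simulated rejection rates (34 patients, at least 2,000 runs per case, REML, nominal 5%, true within-patient slope 0) are:

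| Values per patient | rB 0.7 | rB 0.3 |
|---|---|---|
| 7 | about 30–40% (29–43% over the ICC range and repeated runs) | about 9–10% |
| 35 | 10–12% | 6–7% |

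If values were averaged to one per configuration (3 per patient), the rate at rB 0.7 would be 53–81%.

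Masking, rW = 0.6, rB from 0 to −0.5: the fitted slope is 0.54–0.56 at 7 values and about 0.59 at 35, and the association is detected in essentially every run. Masking is therefore slight here.

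**Check of the remedy.** With patient-mean-centred values, the simulated within-patient correlation is 0.60 when the truth is 0.60 and 0.00 when the truth is 0. The centred slope is rejected in 4.6–6.0% of runs with no within-patient association, at every ICC and number of values tried.

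**The case against.** **The plan nowhere says that raw levels are used.** This is right. A reader might infer it from the plain mention of LV dP/dt, set against the "difference in percentage change dP/dt max from baseline" of 8.1. That contrast is weak evidence: 8.2 and 8.3 also describe the primary endpoint and its analysis as dP/dt max values and differences, although 8.1 defines it as a percentage change. Levels are the literal reading, but the scale is unstated. The missing within/between split does not depend on this, because change scores also differ between patients.

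**A mixed model already removes most of the between-patient component.** This is largely true for a slope. At 35 values the slope is almost purely within-patient, and from 7 values upward a useful sensor would not look useless. The total-correlation figures apply only if that is the coefficient reported, and 8.3 does not say. What the model does not cure is the excess of false positives.

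**The kappa analysis already addresses the within-patient choice.** It does, and a shift in a patient's overall level cannot change which configuration is best in that patient, so kappa is free of this problem. But 6.2.2 lists it as a separate objective, and it uses only each patient's top category. It does not repair the correlation reported for its own objective.

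**The inputs are assumed.** True. The ICC range and rB are not in the documents. An equal ICC may not suit a site-specific measure such as electrical delay, for which the sizes would differ. Conversely, serial correlation between settings would lower the effective number of values and increase the contamination.

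**Conclusion.** The point holds as a gap in method for one secondary objective: the plan's correlation does not isolate the within-patient association that its stated purpose, "to determine the feasibility of using them to guide LV lead placement", requires. The consequence depends on a choice 8.3 leaves open. A total correlation of levels could be badly misleading in either direction over an ICC of 0.5–0.9. For an uncentred random-intercept slope the main risk is a false positive. It is severe with 7 values per patient and strong between-patient correlation, and modest with 35 values or weak between-patient correlation.

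The documents do not support two stronger readings. One is that the sponsor has chosen to correlate raw levels; the text is silent. The other is that the study's overall answer on sensor feasibility will be wrong; the kappa analysis is unaffected, and the mixed model limits masking. The primary non-inferiority comparison and its sample size are not touched.

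**What to change.** In 8.3, for the sensor correlation objective:

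- Enter two terms for each sensor in the model for dP/dt max: the value centred on the patient's own mean, and the patient mean. Include a patient random effect.
- Name the unit of analysis (setting, or setting by AV delay).
- Report the within-patient (repeated-measures) correlation, with its confidence interval, as the result for this objective. The patient-mean term can be shown as descriptive.

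Percentage change from the AAI baseline should not be relied on instead. It still carries differences between patients in average response, and it is not available for the RV-pace-to-LV delay in 7.4.2, because there is no RV pace during AAI pacing.

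The cost is a few lines of text and code, with no new data and no change to the primary analysis. Under the closing text of 8.3, a change of method that leaves the objectives alone needs no amendment, only a description and justification in the study report. Fixing it before the data are analysed also prevents the coefficient from being chosen after the results are seen.
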